**Tobacco**								
Type of tobacco or other products consumed and quantity	X			X		X		X
Nicotine dependence	X			X		X		X
Age at first consumption	X							
Age at start of regular consumption	X							
Previous attempts to stop smoking in their entire consumption trajectory	X							
Previous attempts to quit smoking in the last year	X							
Previous attempts to quit smoking since the last questionnaire				X		X		X
Maximum withdrawal time	X							
Resources used to quit smoking	X		X	X	X	X	X	X
Motivation to quit smoking	X			X		X		X
Smoking cessation provision	X		X	X	X	X	X	X
Efficacy	X		X	X	X	X	X	X
Level of smoking approach received	X	X	X	X	X	X	X	X
Environment	X							
Abstinence from consumption	X		X	X	X	X	X	X

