#### Variables

Dependent variables include tobacco use, cannabis use, and alcohol use. Tobacco use is rated yes/no. If answering “yes”, we ask the about the tobacco consumption pattern, including nicotine dependence using the 6-item Fagerstrom test [35], and the type of tobacco or other products consumed (i.e., cigarettes, roll-your-own tobacco, combination of both, cigars, e-cigarettes, iQOS); smoking history, including the age when the participant starting smoking, maximum abstinence time, previous quit attempts, and resources used (i.e., none, self-help, professional support, pharmacological treatment, etc.); motivation to quit smoking, measured by a Likert scale from 0 to 10; and willingness to quit smoking, assessed by a 4-item questionnaire that, according to Prochaska and DiClemente’s model, classifies smokers into five stages: pre-contemplative, contemplative, preparation, action, and maintenance [36].

Cannabis use is rated yes/no. If “yes”, we recorded users pattern of consumption, problematic use (yes/no) [37], withdrawal symptoms identified using the Marijuana Craving Questionnaire [38] and reasons for use [39]. Alcohol use is rated yes/no and described according to the variables of consumption included in the Alcohol Use Disorders Identification Test (AUDIT) [40, 41]. A fourth dependent variable is participants’ self-reported smoking knowledge, attitude, and services (S-KAS) received during their treatment in SUD programs [42].

The primary outcome is abstinence from smoking (yes/no), which is self-reported and verified by the exhaled CO concentration only if they report to be abstinent. Self-reported abstinence is defined as “no smoking in the 7 days prior to the assessment point.” Seven-day abstinence was chosen as the consumption measure based on the consensus recommendation in practice guidelines for the assessment of abstinence in patients who are not motivated to quit smoking and who may remain abstinent during various periods of the study [43]. Number of quit attempts in the last year of  > 24-h duration [44] were also recorded. All dependent variables are assessed at baseline and 3, 6, and 12 months of follow-up (Table 1).

**Table 1 Tab1:** Study variables and collection time points (at baseline and follow-up)

Variables	Follow-up							
	Baseline	1 week	3 months		6 months		12 months	
			Abstinent	Not abstinent	Abstinent	Not abstinent	Abstinent	Not abstinent

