## Statistical analysis

After finishing the recruitment and follow-up, abstinence and quit attempt incidence rates will be calculated at baseline and at 3, 6, and 12 months according to whether participants have received any type of smoking cessation intervention. We will also calculate the corresponding risk ratios with 95% confidence intervals (CIs) for quitting and quit attempts.

We will assess the association between receiving smoking cessation support and the two primary outcomes (abstinence and quit attempts) using a Poisson regression model with robust variance for several independent variables (the substance of treatment, sex, types of cessation support [e.g., tobacco-related counselling and medication, etc.]), resulting in RRs with their 95% CIs as their estimators. For analysis, we will use SPSS for Windows version 21 with significance set at p  < 0.05.

We will also conduct exploratory factor analysis for testing the psychometric properties of the S-KAS and S-KAP scales.

S3 (months 40–44): Phenomenological study with discussion groups directed towards patients (will be conducted between December 2022 and June 2023).

This qualitative phenomenological study with discussion groups will use a semi-structured script to answer aim 4.

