## Limitations and strengths

A key study limitation may be the limits on extrapolating the findings, as it is complex to understand the use of tobacco and other drugs in a way that represents all SUD clinicians and patients, and we do not know the extent to which the pandemic has affected the attendance of SUD programs. However, the mixed methods design includes several heterogeneous discussion groups for both clinicians and patients with different broad typologies in order to capture a broad range of experiences, barriers, and opportunities and how the pandemic has impacted them. Regarding the questionnaires, self-reported data may include reporting or cognitive biases from participants. Moreover, on account of the patient-professional relationship, selection bias is possible among recruiting clinicians, who could offer the study only to patients who they believe will agree to participate. Lastly, conducting the follow-up interviews by telephone instead of face-to-face may affect the quality of the data collected. However, we had no other option due to the COVID-19 pandemic.

Despite its limitations, the study includes a mixed methods exploratory approach, represents both patient and clinician perspectives, permits triangulation of multiple data sources, and measures primary outcomes (abstinence and quit attempts) in a 1-year follow-up design.

Finally, we strongly believe that the adjustments that were made have allowed us to carry out the study despite the pandemic. Complex observational studies allow the study of real-life phenomena; however, researchers may need to overcome difficulties, such as the COVID-19 pandemic, by introducing innovative strategies to successfully carry out these studies [54]. We are confident that studying tobacco use among the SUD population under these circumstances will allow us to design programs that can be sustained in the real life of clinicians and patients.

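### Quit attempts are called a primary outcome in two places, but Table 1 collects them at follow-up only from participants who are still smoking

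*Protocol article*

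**What the plan says.** All references are to the protocol article.

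- **Status of the outcome.** The Variables section of the cohort of smokers states "The primary outcome is abstinence from smoking (yes/no" and then says that quit attempts were recorded too. The Statistical analysis section refers to "the two primary outcomes (abstinence and quit attempts" and models both against receipt of cessation support. The Limitations and strengths section says that the study "measures primary outcomes (abstinence and quit attempts) in a 1-year follow-up design".
- **Who is asked.** In the Tobacco block of Table 1, "Previous attempts to quit smoking since the last questionnaire" is marked at 3, 6 and 12 months under Not abstinent only; the Abstinent cells are empty. "Previous attempts to quit smoking in the last year" is marked at baseline only. By contrast, "Resources used to quit smoking" is marked in both branches at every one of those visits.
- **What is measured.** The Variables section counts "quit attempts in the last year of" more than 24 hours' duration. The follow-up item instead covers the time since the last questionnaire.
- **When.** The Variables section says "All dependent variables are assessed at baseline and 3, 6, and 12 months of follow-up".
- **What is estimated.** The Statistical analysis section plans incidence rates of abstinence and of quit attempts at each visit by receipt of support, with risk ratios, and a Poisson model with robust variance.

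**The concern.** One of the two stated outcomes decides who is asked about the other. A participant who stops smoking and is abstinent at a visit has made an attempt, but Table 1 does not ask that participant about it. Someone abstinent at all three visits never has a follow-up attempt recorded. Someone abstinent at 3 months and smoking again at 6 months is asked only about the period after the 3-month questionnaire, so the attempt that led to the 3-month abstinence stays unrecorded.

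The planned analysis compares people with and without cessation support. If support is associated with abstinence, the share of attempters who drop out of the record differs between the groups, and the risk ratio for attempts no longer measures what it is said to measure. The unsettled status of quit attempts adds to this: a reader cannot tell whether the affected outcome is primary.

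**Working it through.** **1. Is the gap in Table 1 real?** The row has the same pattern as the other smoker-only rows (nicotine dependence, motivation to quit). The row on resources used to quit is filled in both branches. The pattern is therefore consistent and does not look like a damaged table.

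**2. Size of the distortion at one visit.** The document gives no figure for quit attempts, so there is none to reproduce. For the groups without (0) and with (1) support, let a0, a1 be the proportions abstinent and t0, t1 the true proportions with at least one attempt in the interval. Every abstainer is taken to be newly abstinent and so to count as an attempter.

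- True risk ratio: t1 / t0
- Abstainers coded as no attempt: (t1 − a1) / (t0 − a0)
- Abstainers missing or excluded: [(t1 − a1)/(1 − a1)] / [(t0 − a0)/(1 − a0)]

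Inputs for abstinence come from the Sampling method section: 7 ex-smokers per 100 patient-years, an expected 10 per 100, and a planning relative risk of 2.0. Because 10/7 = 1.43 is not 2.0, both 7% vs 14% and 7% vs 10% are shown. They are used as proportions for illustration. The attempt proportions are assumptions: 30% without support, 30% to 60% with support.

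| Abstinent | True attempts | True RR | Coded no attempt | Excluded |
|---|---|---|---|---|
| 7% vs 14% | 30% vs 30% | 1.00 | 0.16/0.23 = 0.70 | (0.16/0.86)/(0.23/0.93) = 0.75 |
| 7% vs 14% | 30% vs 40% | 1.33 | 0.26/0.23 = 1.13 | (0.26/0.86)/(0.23/0.93) = 1.22 |
| 7% vs 14% | 30% vs 60% | 2.00 | 0.46/0.23 = 2.00 | (0.46/0.86)/(0.23/0.93) = 2.16 |
| 7% vs 10% | 30% vs 60% | 2.00 | 0.50/0.23 = 2.17 | (0.50/0.90)/(0.23/0.93) = 2.25 |

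In the second row the item misses 0.07/0.30 = 23% of attempters without support and 0.14/0.40 = 35% with it. In the last row it misses 23% and 0.10/0.60 = 17%, so the distortion runs the other way. Coding abstainers as no attempt leaves the ratio unbiased only when the abstinence ratio a1/a0 equals the attempt ratio t1/t0, as in the third row.

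**3. What a derivation rule recovers.** Counting new abstainers as attempters restores the yes/no ratio; in the second row, (0.26 + 0.14)/(0.23 + 0.07) = 1.33. It does not restore the number of attempts. A participant abstinent at 3 months who relapses, quits again and is abstinent at 6 months has at least two attempts. The rule credits one, for the first interval, and cannot see the second.

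**4. Recall windows.** The baseline item covers 12 months; the follow-up items cover about 3, 3 and 6 months. Raw proportions at the four time points are therefore not comparable with one another.

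**The case against.** The best defence is that the empty cells are ordinary questionnaire routing. Participants enter as tobacco users, and abstinence means no smoking for 7 days, longer than the 24-hour threshold for an attempt. A yes/no attempt therefore follows from new abstinence, and such a rule could sit in an analysis plan that is not shown. This stands for the yes/no outcome: the bias arises only if abstainers are coded as no attempt or missing, and the article states neither. It does not stand for the number of attempts, which is how the Variables section words the measure, because no later rule can supply an answer that was never asked for.

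The defence can also say that the Variables section lists the dependent variables as tobacco, cannabis and alcohol use plus S-KAS, and asks about previous quit attempts only of those who report tobacco use. That weakens any charge that Table 1 flatly contradicts the stated visit schedule. The tension remains only because later sections promote quit attempts to a primary outcome.

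Four stronger readings are tempting and not supported:

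- A reader might infer that the risk ratio is always pulled towards or below 1. The last row of the table shows that it can rise.
- A reader might infer that only failed attempts are counted. Attempts reported at an earlier non-abstinent visit are kept, including those of people who later succeed.
- A reader might infer six tests at 0.05 and a family-wise error of 1 − 0.95^6 = 26%. The plan does not specify six confirmatory tests, and the two outcomes are plainly related, so independence is not a fair assumption.
- A reader might infer that the Variables section fixes abstinence at 12 months as the primary result. It names abstinence without choosing a visit.

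Unequal recall windows do not bias the risk ratio at a given visit, since both groups share the window; they affect comparisons between visits.

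**Conclusion.** The point holds. As scheduled, quit attempts in any interval that ends in an abstinent visit are not recorded, and the article disagrees with itself on whether quit attempts are primary. Where abstinence differs by support and abstainers are coded as no attempt or left missing, the risk ratio for attempts is biased. In the scenarios shown the error ranges from 1.00 read as 0.70 to 2.00 read as 2.25, with no fixed direction. These sizes rest on assumed attempt proportions and on treating all abstainers at a visit as newly abstinent. Abstinence itself, the outcome that the Variables section names as primary, is not affected by the routing.

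**What to change.** 1. Ask the attempts item in the abstinent branch of the telephone script at 3, 6 and 12 months, with the same 24-hour threshold.
2. For interviews already done, count a participant who is abstinent at a visit but was not at the previous one as having made at least one attempt in that interval, and analyse those data as yes/no. State that further attempts by someone abstinent at two successive visits cannot be recovered.
3. Express attempt rates per person-time, so that windows of about 3, 3 and 6 months can be compared, and reconcile the follow-up item with the last-year definition in the Variables section.
4. Reconcile the Variables, Statistical analysis, and Limitations and strengths sections so that abstinence is the primary outcome and quit attempts are secondary.

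The cost is one extra question in an existing call, a derivation rule and some wording. At submission 98 participants had been recruited against a revised target of at least 200 to 250, so much of the follow-up could still be collected in the corrected form.

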**Cannabis**								
Consumption once in lifetime	X		X		X		X	
Consumption in the last month	X		X	X	X	X	X	X
Frequency of cannabis use in the last month	X			X		X		X
Problem cannabis use (only for patients under treatment for alcohol abuse)	X		X	X	X	X	X	X
Frequency of use, consumption, and interaction with tobacco in the last 30 days	X		X	X	X	X	X	X
Context of cannabis smoking	X			X		X		X
Latest consumption	X		X	X	X	X	X	X
Age at start of consumption	X							
Reasons for cannabis use	X							
Previous attempts to stop using cannabis	X							
Maximum withdrawal time	X							
Resources used to stop using cannabis	X							
Willingness to quit cannabis use	X		X	X	X	X	X	X
Motivation to quit cannabis use	X			X		X		X
Efficacy	X		X	X	X	X	X	X
Environment	X							
**Alcohol**								
Alcohol consumption in the last month	X		X	X	X	X	X	X
Problem alcohol use (only patients receiving cannabis dishabituation)	X							
Context of alcohol drinking	X							
Latest consumption	X		X	X	X	X	X	X
Age at start of consumption	X							
Reasons for alcohol consumption	X							
Previous attempts to stop drinking alcohol	X							
Maximum withdrawal time	X							
Resources used to stop drinking alcohol	X							
Willingness to quit alcohol	X		X	X	X	X	X	X
Motivation to quit alcohol	X			X		X		X
Efficacy	X		X	X	X	X	X	X
Environment (family, friends, etc.)	X							
**Psychiatric diagnostic**								
Suicide risk	X				X	X		
Quality of life	X				X	X	X	X
Self-perceived health status	X		X	X	X	X	X	X
Sociodemographic	X							
**Primary outcome**								
Breathed CO concentration	X		X	X	X	X	X	X

Independent variables include sociodemographic data (sex, age, employment status and occupation, and education level), self-perceived state of health addressed by the question “How would you say your general health is?”, measures of mental and physical health according to the DSM-V [45], quality of life according to the General Health Questionnaire (GHQ-12) [46], and level of previous smoking cessation treatment received using questions about standard interventions included in the Smoking Cessation Guidelines (i.e., advice, reduction recommendation, educational material, cognitive-behavioral treatment, pharmacological treatment, nothing) [47].

#### Instrument

Baseline and follow-up questionnaires have been designed including all variables and their dimensions described above. These questionnaires are based on the findings of the discussion groups with clinicians and an extensive literature research. The backwards translation of the S-KAS [42] and the Marijuana Withdrawal Questionnaire from English to Spanish was performed by two Spanish native speakers. All data are entered into a computer software designed for the ACT-ATAC project for the introduction and management of patient data. The software allows recruitment and recording of initial variables by the clinician, and introduction of the results of the questionnaire interviews carried out by the field nurse. The initial and follow-up questionnaires (6 and 12 months) are not accessible by the clinician.

### Cohort of clinicians

#### Participants

Clinicians from the province of Barcelona who agree to participate in the study must meet the following inclusion criteria: (1) to be a clinician (psychologist, psychiatric, nurse, social worker, etc.) in one of the public SUD programs in the province of Barcelona, and (2) that does the initial assessment and follow-up of persons with alcohol and/or cannabis abuse disorders, and (3) provides consent. The exclusion criterion is an inability to guarantee a 12-month follow-up (due to anticipated moves, etc.). We expected to include between 20 and 30 clinicians, and 22 clinicians are currently collaborating in the study from 10 different SUD centers.

#### Variables

The primary dependent variable is self-reported smoking knowledge, attitude, and practice (S-KAP) [48] during the clinician’s work in the SUD program, monitored at baseline of their participation, one week after, and every three months during their participation in the study.

Independent variables are tobacco consumption (never user, former user, and current user), sociodemographic data (sex, age, education level, profession), and professional experience (years treating drug abuse population, years working in the same program). In the case of being a tobacco user, we ask about the tobacco product consumed (i.e., cigarettes, roll-your-own tobacco, combination of both, cigars, e-cigarettes, iQOS); smoking history, including age when starting smoking, maximum abstinence time, previous quitting attempts, and resources used (i.e., none, self-help, professional support, pharmacological treatment, etc.); motivation to quit smoking, measured by a Likert scale from 0 to 10; and willingness to quit smoking, assessed by a 4-item questionnaire according to Prochaska and DiClemente’s model, classifying smokers into five stages of change [36].

Clinicians receive the KAP questionnaire [48] every three months to report data on the approach taken in the care of the smoker (ask, advise, assist).

## Statistical analysis

After finishing the recruitment and follow-up, abstinence and quit attempt incidence rates will be calculated at baseline and at 3, 6, and 12 months according to whether participants have received any type of smoking cessation intervention. We will also calculate the corresponding risk ratios with 95% confidence intervals (CIs) for quitting and quit attempts.

We will assess the association between receiving smoking cessation support and the two primary outcomes (abstinence and quit attempts) using a Poisson regression model with robust variance for several independent variables (the substance of treatment, sex, types of cessation support [e.g., tobacco-related counselling and medication, etc.]), resulting in RRs with their 95% CIs as their estimators. For analysis, we will use SPSS for Windows version 21 with significance set at p  < 0.05.

We will also conduct exploratory factor analysis for testing the psychometric properties of the S-KAS and S-KAP scales.

S3 (months 40–44): Phenomenological study with discussion groups directed towards patients (will be conducted between December 2022 and June 2023).

This qualitative phenomenological study with discussion groups will use a semi-structured script to answer aim 4.

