#### Sampling method

The incidence of unassisted smoking cessation is seven ex-smokers per 100 patient-years [33]. We estimate that, among this sample, being in contact with the health system may increase this rate to 10 ex-smokers per 100 patient-years (i.e., a relative risk [RR] of quitting smoking of 2.0). Therefore, to detect this RR assuming an alpha error of 5%, a beta error  < 20%, and losses of 20%, we require 366 participants. The sample size was calculated using the GRANMO program [34]. This sample size is achievable in one year as the 48 centers in the province of Barcelona treat approximately 5000 new cases for alcohol and 1500 new cases for cannabis yearly (target population: 6,500 participants) [12]. On average, the 10–12 selected study centers should treat approximately 1,625 people/year. Smokers in treatment for alcohol and/or cannabis use are being recruited consecutively for one year.

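### The article names one primary outcome under Variables but two under Statistical analysis and Limitations, and it fixes no deciding visit

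*Protocol article*

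**What the plan says.** Three sections of the protocol article describe what is primary.

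- **Cohort of smokers, Variables.** The singular is used: "The primary outcome is abstinence from smoking (yes/no), which is self-reported and verified by the exhaled CO concentration" in those who report abstinence. Abstinence means no smoking in the 7 days before the assessment point. Quit attempts follow as an item also recorded ("Number of quit attempts in the last year of" more than 24 hours' duration), without the word primary. Dependent variables are assessed at baseline and at 3, 6 and 12 months.
- **Statistical analysis.** The plan is to assess the "association between receiving smoking cessation support and the two primary outcomes (abstinence and quit attempts) using a Poisson regression model with robust variance". Before that, "abstinence and quit attempt incidence rates will be calculated at baseline and at 3, 6, and 12 months" according to whether any cessation intervention was received, with corresponding risk ratios and 95% confidence intervals for both outcomes. One general threshold is given: "we will use SPSS for Windows version 21 with significance set at p < 0.05".
- **Limitations and strengths.** The plural returns: the study "measures primary outcomes (abstinence and quit attempts) in a 1-year follow-up design".

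The Sampling method section gives the only design calculation. It concerns the rate of becoming an ex-smoker per 100 patient-years: "to detect this RR assuming an alpha error of 5%, a beta error < 20%, and losses of 20%, we require 366 participants". Quit attempts play no part in it.

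**The concern.** The primary outcome is the one result that readers should be able to identify before the data are seen. Here, one section lets abstinence alone decide, while two others let quit attempts share that role. With no deciding visit fixed, abstinence or quit attempts at 3, 6 or 12 months could each be put forward as the primary result.

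These results can disagree. Support might go with more quit attempts at 3 months and with no more abstinence at 12 months, and the text as it stands would allow either to be reported as the main answer. The Discussion intends the findings to inform future intervention programmes in the Spanish healthcare system, so the choice should not be left open until the results are known.

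**Working it through.** **Step 1. Set the statements side by side.**

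| Section | Primary outcome(s) | Deciding visit |
|---|---|---|
| Variables | Abstinence; quit attempts also recorded | None (baseline, 3, 6, 12 months listed) |
| Sampling method | Quitting only, per 100 patient-years, alpha 5% | None named |
| Statistical analysis | Abstinence and quit attempts | None (baseline, 3, 6, 12 months listed) |
| Limitations and strengths | Abstinence and quit attempts | None named; 1-year follow-up mentioned |

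The per-patient-year sizing and the 1-year follow-up point towards abstinence at 12 months, but no section says so.

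**Step 2. The plan's own figures.** The article states no error rate across outcomes or visits, so there is none to reproduce. Its only design figure is 366 participants. That figure concerns a single outcome and is not used below. As a check, 7% against 14% (the stated RR of 2.0), two-sided 5%, 80% power, gives

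n per group = [1.96 × √(2 × 0.105 × 0.895) + 0.842 × √(0.07 × 0.93 + 0.14 × 0.86)]² / 0.07² ≈ 300,

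so 600 in total and 600 / 0.8 = 750 with 20% losses. The 366 does not reproduce as a total, and the stated rates of 7 and 10 give a ratio of 10/7 = 1.43 rather than 2.0. That is a separate matter.

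**Step 3. Chance of at least one false positive.** Inputs:

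- 5% per test, from the article; two-sided is assumed from the 95% intervals.
- k = 2 (two outcomes at one visit) or k = 6 (two outcomes × three follow-up visits).
- A common correlation ρ between the test statistics. The article gives none, so a range is shown.

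For independent tests:

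- k = 2: 1 − 0.95² = 9.75%
- k = 6: 1 − 0.95⁶ = 26.5%

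For correlated normal statistics with c = 1.96 and U standard normal:

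1 − E_U{[Φ((c − √ρ·U)/√(1−ρ)) − Φ((−c − √ρ·U)/√(1−ρ))]^k}

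For the favourable direction only, the second Φ term is dropped. With independence this gives 1 − 0.975² = 4.9% and 1 − 0.975⁶ = 14.1%.

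| ρ (assumed) | k = 2, either direction | k = 2, favourable | k = 6, either direction | k = 6, favourable |
|---|---|---|---|---|
| 0 | 9.8% | 4.9% | 26.5% | 14.1% |
| 0.5 | 9.1% | 4.5% | 20.7% | 10.4% |
| 0.8 | 7.8% | 3.9% | 13.9% | 6.9% |
| 0.9 | 7.0% | 3.5% | 10.8% | 5.4% |

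The references for a single test are 5% in either direction and 2.5% in the favourable direction.

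**The case against.** Four points on the other side deserve weight.

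- **Six formal tests are not documented.** The Statistical analysis section plans rates and risk ratios with confidence intervals at each visit, which is estimation. It does not say at which visit the Poisson model is fitted, or that it is fitted three times, and the p < 0.05 threshold is one general sentence. This stands: the k = 6 columns show what follows if every interval is read as a test. The two primary outcomes are documented.
- **Error control may sit elsewhere.** A condensed article may leave a testing hierarchy or alpha split to an analysis plan that is not shown. This also stands, and the absence of such a rule is not held against the article. It does not excuse sections of the same article that disagree on how many primary outcomes there are.
- **The study is observational and partly exploratory.** The aims are to describe changes and identify predictors, and the article speaks of association. This lowers the stakes and argues against insisting on strict family-wise control. But the word exploratory describes the mixed-methods approach, whereas these outcomes are called primary and carry a significance threshold and a formal sample size.
- **The size depends on an unstated correlation.** True, which is why a range is given.

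A reader might infer that the chance of wrongly concluding that support works is about 20% instead of 5%. The documents do not support that. The 20.7% requires six tests and an assumed correlation of 0.5, and it counts false positives in both directions. The favourable-direction figure in that setting is 10.4%, against 2.5% for one test. A reader might also multiply by the types of support, but the article enters these as model variables, gives no number of types and plans no separate test per type and visit.

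**Conclusion.** The inconsistency is real: one primary outcome in Variables, two in Statistical analysis and in Limitations and strengths, no deciding visit anywhere, and a sample size that rests on quitting alone.

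Its size on the documented reading is modest. Two primary outcomes at one visit raise the chance of some false positive from 5% to between 7% and 10%. If all three follow-up visits are also read at p < 0.05, the range is about 11% to 26%, roughly half of it favourable. Both ranges assume two-sided tests and a common correlation between 0 and 0.9, and the second also assumes that the model or intervals are used as tests at each visit. The labelling contradiction needs no such assumption and should be corrected before analysis.

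**What to change.** - In Statistical analysis, name one primary contrast: any cessation support versus none, on 7-day abstinence at 12 months, tested two-sided at 5%.
- In Statistical analysis and in Limitations and strengths, call quit attempts a secondary outcome, so that both agree with Variables and with the outcome behind the sample size.
- Label the 3- and 6-month risk ratios and the individual support types as secondary or exploratory, and report them with 95% confidence intervals.

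This takes a few sentences and needs no new data or participants. The one small cost is that quit attempts and the earlier visits can no longer carry a stand-alone primary claim.
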